## Appendix B – Patient Identification Card (intervention only)

| **Participant Name:**  **Please Contact CLD Nurse:**  Phone Number (within hours): | **Research Trial – ALFIE**  This patient is participating in a study investigating a new way of managing patients with cirrhosis of the liver – Chronic Disease Management.  As part of this study this patient is receiving case management for their liver disease and their case coordinator would appreciate being informed of any admission to hospital or symptoms of concern related to the liver.  If you require information please call the number provided. |
| --- | --- |

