## Control/usual care group

Control/usual care patients will continue hospital and out of hospital management via usual care processes. To prevent contamination of usual care patients by the intervention, usual care patients will have no contact with CLD nurses until a final end of study interview. Usual care patients will be mailed surveys at baseline, 3 months, 6 months, and then 6-monthly until the end of the trial (24 months after the first patient randomised). At the end of the trial, control group participants are invited for a face-to-face review to complete the surveys, are given the Cirrhosis Booklet and offered an education session.

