## Home Visit

Intervention participants will have a home visit from the trial nurse booked within 7 days of hospital discharge. At this point the care plan is further discussed with the patient and interventions agreed upon with the patient. The home visit is an opportunity to increase rapport and develop your clinical relationship and trust, to assess patient risk, and assess their physical state and symptoms after discharge from hospital. Although some issues such as medication management can start to be addressed in hospital, it is only at the home visit that the nurse can really assess how the participant manages their medications. The home visit will only be provided to patients in the Metropolitan area.

Prior to the home visit, ensure you complete your site’s home visit risk assessment form as local protocol requires. If the risk assessment shows unacceptable risk the visit is not to take place and the home visit procedures conducted over the phone.

If risk is acceptable, at the home visit, complete the ALFIE Study home visit form. It is envisaged that the home visit will take 30-60 minutes. Time the visit and enter the duration of the visit on the Home Visit form (Appendix I). Complete a full report of the visit in the participant’s case note as a record of your findings and to record the plan.

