## Outpatient review by Specialist Gastroenterologist/Hepatologist

Review by a specialist must be scheduled within 1 month (4 weeks) of discharge from hospital for all patients in the intervention group. The nurse must attend this appointment with the patient. In preparation for the outpatient appointment the following should be updated:

- - Medication list
  - Care Plan
  - Ensure screening and surveillance requirements are up to date (or booked)

At this appointment the specialist will discuss the care plan with the nurse and the patient and sign off on the care plan.

## Month 3, Month 6, Month 12, Month 18

Patients in the intervention group have their Child Pugh and Meld scores completed at 3, 6, 12, 18 months and at end of trial (Appendix N). Collect the information from the most recent bloods taken as part of usual care, the patient will not be required to have a blood test taken just for this score to be done.

Surveys are due for both groups at this time. For intervention patients this should ideally be scheduled at the same time the specialist outpatient appointment is scheduled to enable accurate determination of the Child Pugh and MELD score. Ensure the contact log is up to date. Patients will be provided the option of receiving the surveys via standard post or electronically, via email, at consent.

Record hospital and liver-related outpatient admissions/attendances/non attendances at the month 12 visit.

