# Outcomes

## Unplanned liver-related hospital admission rate

Unplanned liver-related hospital admission rate will be the primary outcome measure of the trial. Other hospitalization measures, as outlined in the Aims section, will be measured as secondary endpoints.

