## Incremental cost effectiveness relative to usual care and quality of life

The economic evaluation will be carried out to assess the incremental cost effectiveness of the CDM model, relative to usual care, for patients with decompensated cirrhosis over the study duration. The primary economic outcome will be the incremental cost per unplanned admission avoided in the intervention arm relative to the usual care arm. Secondary economic outcomes will include the incremental cost per death prevented and incremental costs per quality adjusted life year (QALY) gained. QALYs will be based on responses to the EuroQoL 5 dimensions 5 level (EQ5D 5L) and a validated disease specific Chronic Liver Disease Questionnaire (CLDQ)([43](#_ENREF_43)).

Incremental costs associated with the intervention compared to usual care over the study period will be estimated using Medical Benefits Schedule (MBS) and Pharmaceutical Benefits Schedule (PBS) data to estimate primary care, pharmaceutical, and private hospital costs, and centralised costing data for inpatient episodes at public hospitals (Australian Refined Diagnosis Related Groups (AR-DRGs) cost weights). Consent to access PBS/MBS/AR-DRG data will be sought from recruited patients. Intervention specific costs (e.g. labour costs, travel and telephone expenditure etc) will be collected administratively within the trial. Patient level measures of utility derived from the EQ-5D 5L and CLDQ instruments (measured at baseline 3 and 6 months then 6-monthly in the intervention group and at the end of trial in both groups) will be integrated with survival curves in order to calculate QALYs over the study period. This economic evaluation will include cost-effectiveness, acceptability, net benefit and expected net loss curves to inform decision makers of the optimal strategy at any given threshold, and uncertainty around this decision.

At the end of the study, both groups will be asked to complete a short resource use questionnaire asking patients to share how much time and money have been spent on health care over the past 2 weeks.

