# Statistical Methods

## Sample size and power analysis

The trial will be powered for the primary endpoint of unplanned liver-related admissions. Assuming an admission rate of three admissions per person per year in the usual care group, and a reduction of 20 % in the treatment group, a sample size of 146 (50 per site) would provide 80% power to detect a significant difference in event rates between groups at a type 1 error rate of α=0.05. This assumes a median follow-up time of 18 months, as well as allowing for a 20% attrition rate throughout the trial. Recruitment of a sample size of 147 patients within 12 months is feasible and represents approximately 38 patients per site. The anticipated caseload of intervention patients per site is 19, which was less than the caseload during the pilot trial (40) and will be feasible with a 0.6 fte RN level 3 nurse at each site.

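### Admissions for the primary outcome could be captured more completely in the intervention arm, because the protocol fixes no common source for finding them

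*Protocol*

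**What the plan says.** The Outcomes section states: "Unplanned liver-related hospital admission rate will be the primary outcome measure of the trial". It does not say how admissions are to be found.

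Contacts that exist in the intervention arm only:
- An identification card for use in emergency departments, GP practices and other services (The Chronic Disease Management Model). It tells them that "their case coordinator would appreciate being informed of any admission to hospital" (Appendix B).
- GP communication at admission or discharge (Role of General Practitioner; note a to the intervention activity schedule).
- Nurse calls, weekly for three months and then less often, and face-to-face contact at Months 3, 6, 12, 18 and 24 (intervention activity schedule).

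For controls, "usual care patients will have no contact with CLD nurses until a final end of study interview" (Control/usual care group). They are mailed surveys in the meantime.

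Recording of admissions:
- The section on Months 3 to 18 says: "Record hospital and liver-related outpatient admissions/attendances/non attendances at the month 12 visit". Both activity schedules mark admissions at Month 12 and at the end of study.
- Appendix J records dates, reason, liver-related status, emergency or elective status and intensive care days. The reason comes from the discharge summary. The form does not say which hospitals or records are searched or who fills it in, and it has no field for the hospital.
- Appendix Q lists the admissions form among the items to check for a patient who completed the study.

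The economic section plans to use "centralised costing data for inpatient episodes at public hospitals", with consent, but only for costing.

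**The concern.** A count outcome is comparable between arms only if events are looked for in the same way. Here one arm has several routes by which the nurse can learn of an admission to another hospital, and the other has none before the final interview. The Month 12 recording in controls is attached to a visit that the control section rules out, so it has to be done from records whose scope is not stated.

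Death sharpens the problem. The Background cites two-year survival of 60% in Child-Pugh B and 35% in Child-Pugh C. If those figures applied here, 40% to 65% of patients would die within two years, and Appendix Q does not ask for the admissions form in patients who die. A control who dies never reaches the final interview, whereas an intervention patient who dies has had nurse contact before.

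Outside admissions are plausible, since "The home visit will only be provided to patients in the Metropolitan area" implies that some patients live elsewhere. At stake is a real reduction in admissions that appears smaller than it is. The primary economic outcome, cost per unplanned admission avoided, would presumably rest on the same count.

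**Working it through.** **Inputs from Sample size and power analysis.** "Assuming an admission rate of three admissions per person per year in the usual care group", and "a reduction of 20 % in the treatment group". This gives 3.0 and 2.4 admissions per person-year, a ratio of 0.80. Also: N = 146, 80% power, α = 0.05 (taken as two-sided), median follow-up 18 months, attrition 20%.

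**The plan's own figure.** Poisson, log rate ratio: n per arm = (1.96 + 0.84)² × (1/(3t) + 1/(2.4t)) / (ln 0.80)².
- t = 1.5 years: 79 per arm, 158 in total, and 158/0.8 = 198 after attrition. This does not reproduce 146.
- t = 2 years: 60 per arm, 120 in total, and 120/0.8 = 150 after attrition (148 with the rate-difference form). This is within about 3% of 146.

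That mismatch is a separate matter. I use the variant that fits: 146/2 × 0.8 = 58.4 patients per arm for 2 years, without overdispersion.

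**Bias from unequal capture.** Let s be the share of admissions outside the trial hospital, and c_I and c_C the fractions of those captured in the intervention and control arms. Overall capture is r_I = 1 − s + s·c_I and r_C = 1 − s + s·c_C.
- Observed ratio = 0.80 × r_I / r_C = 0.80/(1 − f), with net control under-capture f = 1 − r_C/r_I.
- SE = √[(1/(3·r_C·2) + 1/(2.4·r_I·2)) / 58.4].
- Power = Φ(−ln(observed ratio)/SE − 1.96).

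The protocol gives neither s nor the capture fractions, so every value of s, c_I and c_C below is an assumption.

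| s | c_I vs c_C | f | Observed ratio | Power |
|---|---|---|---|---|
| any | equal, 100% | 0 | 0.80 | 79% |
| 5% | 100% vs 75% | 1.25% | 0.81 | 75% |
| 5% | 100% vs 50% | 2.5% | 0.82 | 69% |
| 10% | 100% vs 50% | 5% | 0.84 | 56% |
| 20% | 90% vs 60% | 6.1% | 0.85 | 50% |
| 20% | 100% vs 50% | 10% | 0.89 | 30% |
| 30% | 100% vs 50% | 15% | 0.94 | 11% |
| 20% | 100% vs 0% | 20% | 1.00 | 2.5% |

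**Check in counts.** Expected admissions are 58.4 × 3 × 2 = 350 in controls and 58.4 × 2.4 × 2 = 280 in the intervention arm. Losing 5% of the control admissions (about 18) gives 280/333 = 0.84. Losing 10% (about 35) gives 280/315 = 0.89.

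**Equal but incomplete capture.** If both arms capture 90% of outside admissions, the ratio stays at 0.80 and power is 78% to 79% for s from 5% to 30%. The harm comes from unequal capture and hardly at all from incomplete capture.

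**The case against.** The strongest reply is that the protocol treats the arms alike where it matters: one form, the same two time points, and fields (medically stable date, discharge-summary reason, intensive care days) that come from records. The card, calls and GP contact are described as care. The nurse contact log has no admission field, GP contact is mainly outgoing, and weekly calls are required for only three of 24 months. All of this stands, and it limits the claim to what could happen. It does not supply the missing statement of which records are searched, in which hospitals, for which patients.

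A reader might infer more than the documents support:
- That admissions are in fact found through the intervention-only contacts. No section says so.
- That control admissions rest on long recall. The form points to records, and nothing in the text provides for recall.
- That the pilot's trend to more hospitalisation was this bias. The increase reported in the Background was in liver-related bed days (17.8 vs 11.0 per person-year). Unplanned admissions, the closer outcome, fell by a non-significant 21%.
- That many patients are admitted elsewhere. The home-visit rule gives no number of non-metropolitan patients and does not say where they are admitted.

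A fair point against the remedy is that the costing data are not said to carry emergency or liver-related status. The log fields and discharge summaries therefore remain necessary.

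**Conclusion.** The concern holds as a gap in the design, not as demonstrated bias. The routes for learning of admissions differ by arm, no arm-independent source is fixed for the primary outcome, and Appendix Q does not require the log for patients who die. If control admissions are under-captured as a result, the rate ratio moves towards no effect.

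With a true ratio of 0.80, a net control under-capture of 5% gives 0.84 and one of 10% gives 0.89. Power then falls from about 79% to 56% and 30%. These powers assume Poisson counts, two years of follow-up and 20% attrition. Overdispersion, which the planned negative binomial model allows for, would lower all of them.

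The size cannot be derived from the protocol. If 5% of admissions are outside and half of those are missed in controls only, the ratio is 0.82. Losing the whole effect needs an extreme case, such as 20% outside with none found in controls and all found in the intervention arm.

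**What to change.** Amend the section on Months 3 to 18, the primary outcome paragraph, Appendix J and Appendix Q before outcome data are compiled:
- Identify admissions in both arms from the same sources: trial-hospital records plus the centralised public-inpatient data already planned for costing.
- Use the same period in both arms, from randomisation to death, transplant listing or end of follow-up. Include patients who die or withdraw, subject to consent.
- Replace the Month 12 visit, for this purpose, with a record-based extraction in both arms. Add fields for hospital and source to Appendix J, and require the log in Appendix Q whatever the patient's outcome.
- Request the discharge summary for every listed episode, so that the blinded assessor foreseen in the randomisation and blinding section can classify emergency and liver-related status.
- Leave admissions known only through nurse, GP or card contact out of the primary analysis unless they appear in those sources. Report them in a sensitivity analysis.

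The cost is protocol wording, some extra data handling and wider use of an extract already planned. Admissions outside these sources, for example to private hospitals, are missed, but by a rule that does not depend on arm.

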## Appendix C – Ascites and Hepatic Encephalopathy Assessment

**Timepoint Assessment Completed:**  Baseline (intervention only) - Date: ___ / ___/ __

End of Trial - Date: ____ / ____/ _____

| ***ASCITES*** | | **Yes** | **No** |
| --- | --- | --- | --- |
| 1 | Does the patient have or ever had ascites?  If yes, add to care plan and continue with questions below.  If no, go to HE assessment. |  |  |
| 2 | If yes, is the patient on diuretics? (if yes, add to medication chart) |  |  |
| 3 | Action Plan given to patient and discussed |  |  |
| 4 | Weight chart discussed |  |  |
| 5 | Does patient have digital scales? (if no, add to care plan) |  |  |
| 6 | Any prior episode of spontaneous Bacterial Peritonitis (if yes, add to Care Plan) |  |  |
| 7 | Any evidence of prior total protein level in ascitic fluid ≤ 10g/L? |  |  |
| 8 | Is patient prescribed SBP prophylaxis? (If yes, add to medication list) |  |  |

Comments:

| ***HEPATIC ENCEPHALOPATHY*** | | **Yes** | **No** |
| --- | --- | --- | --- |
| 1 | Has patient ever had diagnosis of HE? (If yes, add to care plan and continue with below) If no – go to question 6. |  |  |
| 2 | Is patient on lactulose? (ensure on medication chart) |  |  |
| 3 | Is patient on rifaxamin? (ensure on medication chart) |  |  |
| 4 | Action plan for HE discussed |  |  |
| 5 | Does the patient drive? (if yes, ensure fitness to drive reviewed) |  |  |
| 6 | Number connection test done SCORE: ________________ seconds |  |  |
| 7 | EncephalApp assessment done SCORE: ___________________ |  |  |
| 8 | Does the patient have minimal HE? |  |  |

Comments:

## Appendix D – Osteoporosis Assessment

**Timepoint ASSESSMENT COMPLETED:**  Baseline - Date: ____ / ____/ _____

End of Trial - Date: ____ / ____/ _____

| ***Osteoporosis*** | | **Yes** | **No** |
| --- | --- | --- | --- |
| 1 | Has the patient had a Bone Density Scan (DEXA)? (if no, add to care plan to refer for screening) |  |  |
| 2 | What was the outcome of the most recent DEXA? (complete when DEXA done)  Normal  Osteopenia (add to care plan, confirm supplements started and add to medication chart)  Osteoporosis (add to care plan, confirm supplements and treatment started and add to medication chart) |  |  |
| 3 | Has patient had a vitamin D level taken? (if no add to care plan) |  |  |
| 4 | Outcome of last vitamin D level?  Normal  Mildly deficient (add to care plan, confirm supplements started and add to medication chart)  Severely deficient (add to care plan, confirm supplements started and add to medication chart) |  |  |
| 5 | If patient has osteoporosis/osteopenia are they on appropriate bone treatment? (ie vitamin D and calcium supplementation if osteopenic, Vitamin D and bisphosphonate if osteoporotic)  If No, please comment on why: |  |  |

Comments:

## Appendix E – Alcohol Assessment

**Timepoint ASSESSMENT COMPLETED:**  Baseline - Date: ____ / ____/ _____

End of Trial - Date: ____ / ____/ _____

| ***Alcohol use – prior to today’s assessment*** | | **Yes** | **No** |
| --- | --- | --- | --- |
| 1 | Has the patient drunk any alcohol in the last 6 months? (if yes, put on care plan) |  |  |
| 2 | If abstinent, date of last drink of alcohol (month and year) ______ / _______  month / year |  |  |
| 3 | If yes, specify alcohol amount:  Last 6 months:  Light (<2/day)  Moderate (2-4/day)  Heavy (>4/day)  Last 2 weeks:  Nil  Light (<2/day)  Moderate (2-4/day)  Heavy (>4/day) |  |  |
| 4 | Has patient seen Drug and Alcohol Services? (if no, arrange during inpatient stay) |  |  |
| 5 | Has an anticraving agent been prescribed? (If yes, add to medication list) |  |  |
| 6 | Is an anticraving agent being taken? (check with patient) |  |  |
| 7 | Has patient been referred to a psychologist for CBT/counselling? ( If no, add to plan of care for MHCP with GP and referral to psychologist) |  |  |

Comments:

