## Secondary Objectives

- To evaluate incremental cost effectiveness for this intervention, relative to usual care. Assessment of quality of life will be a necessary component of the economic analysis. The QALY will be used to assess this outcome.
- To evaluate the effect of CDM on mortality
- To evaluate the effect of CDM on the quality of care provided to patients in the intervention arm. This will be assessed using the following measures:
  - attendance at planned outpatient care;
  - medication adherence;
  - adherence to antibiotic prophylaxis protocols for patients with ascites;
  - adherence to variceal bleeding prevention protocols;
  - adherence and response to alcohol abuse treatment protocols in alcoholic liver disease patients; and
  - referral rates to liver transplantation assessment teams.
- To compare self-management ability and knowledge of patients in the CDM arm with usual care models.

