## Appendix F – Variceal Management Assessment

**Timepoint ASSESSMENT COMPLETED:**  Baseline - Date: ____ / ____/ _____

End of Trial - Date: ____ / ____/ _____

| ***VARICES*** | | **Yes** | **No** |
| --- | --- | --- | --- |
| 1 | Has the patient had an Endoscopy? (if no, add to care plan to refer for screening) |  |  |
| 2 | Has the patient ever had a variceal bleed? (If yes, add to care plan) |  |  |
| 3 | Confirm education given regarding variceal bleeding cause and prevention |  |  |
| 4 | Assessment of eligibility for Baveno VI Criteria  Fibroscan < 25kPa – Date fibroscan done __ / __ / ____  Platelets > 110 – Platelet level ______ Date __ / __ / ____  If fibroscan not done, ensure this is on the care plan |  |  |
| 5 | What was the date and outcome of the most recent endoscopy?  Date: ____ / ____/ _____  No varices  Small varices (<5mm, or Grade 1 or 2)  Large varices/High risk varices (>5mm, or Grade 3)  No endoscopy done  Endoscopy not required due to Baveno VI criteria |  |  |
| 6 | According to the outcome above and the protocol for variceal screening and surveillance, what is the plan of care? (ensure add to care plan and recalls)  Baveno VI criteria – fibroscan due ____ / ____ /_______  Endoscopy in 3 years due ____ / ____ /_______  Endoscopy in 2 years due ____ / ____ /_______  Endoscopy in 1 year due ____ / ____ /_______  Variceal Ligation (eradication) ____ / ____ /_______  TIPS done ____ / ____ /_______  Primary prophylaxis (please add to medication chart and care plan)  Secondary prophylaxis post variceal bleed (please add to medication chart and care plan) |  |  |
| 7 | Was the patient adherent to variceal bleeding prevention protocols (answer only at end of trial) |  |  |
| 8 | Prophylaxis – primary or secondary  What is the patient’s pulse rate? ____________ bpm  (ensure that the patient is resting comfortably for 10 minutes prior to taking pulse rate) |  |  |

Comments:

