## Appendix R – HCC Assessment form

**Timepoint Ax COMPLETED:**  Baseline (intervention only) - Date: ____ / ____/ _____

End of Trial - Date: ____ / ____/ _____

| ***HCC*** | | **Yes** | **No** |
| --- | --- | --- | --- |
| 1 | Has the patient had an upper abdominal ultrasound? (if no, add to care plan to refer for screening) |  |  |
| 2 | How many ultrasounds has the patient had the last 2 years  0  1 Date : ____ / ____/ _____  2 Date : ____ / ____/ _____  3 Date : ____ / ____/ _____  4 Date : ____ / ____/ _____  N/A – patient only just diagnosed with cirrhosis (baseline only option) |  |  |
| 3 | Was HCC found in any of the above ultrasounds? |  |  |

Comments:

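### At end of trial, the alcohol-treatment items on Appendix E (chiefly items 4 and 7) have no start point and no date, so a truthful Yes can describe care given before randomisation

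*Protocol*

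**What the plan says.** The protocol's Secondary Objectives list, among the quality-of-care measures, "adherence and response to alcohol abuse treatment protocols in alcoholic liver disease patients". The section on quality of care indicators says these will be measured. The Statistical methods section plans to compare quality indicators between groups by negative binomial regression.

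Appendix E is one form for two time points, baseline and end of trial. Its table heading reads "Alcohol use – prior to today’s assessment", which gives an end to the period but no beginning. The items differ in how they treat time:

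- Items 1 and 3 (drinking) use windows of 6 months and 2 weeks. Item 2 asks for the month and year of the last drink.
- Item 4 asks "Has patient seen Drug and Alcohol Services? (if no, arrange during inpatient stay", with no window and no date.
- Item 5 asks "Has an anticraving agent been prescribed? (If yes, add to medication list", with no window and no date on this form.
- Item 6 asks "Is an anticraving agent being taken? (check with patient", which is a question about current use.
- Item 7 asks whether the patient has been referred to a psychologist, with no window and no date.

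The End of Study section and both activity schedules require the alcohol assessment at end of study in both arms. At baseline it appears only for the intervention arm, after randomisation.

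**The concern.** Care received before randomisation cannot be an effect of the intervention. An unbounded question about whether a patient has seen a service is truthfully answered Yes for a contact years before enrolment. Item 4's own instruction, to arrange the contact during the inpatient stay, suggests wording written for baseline care planning and reused at the end of the trial.

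If such answers enter the between-arm comparison, both arms carry an added block of Yes answers unrelated to the trial. A real gain in alcohol care during follow-up could then look small or absent. The gap lies in data collection: a later analysis plan can choose how to score the items, but it cannot restore dates that were never recorded.

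**Working it through.** The protocol states no rate, difference or power for this measure, so there is no figure to reproduce. The check has two parts.

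**1. Can earlier care be removed with other data in the protocol?**

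| Possible source | What it offers | Enough? |
|---|---|---|
| Baseline Appendix E | Intervention arm only, after randomisation; control schedule marks it only at Month 24/EOS | No. Removing earlier care in one arm alone would bias the comparison against the intervention |
| Appendix K (outpatient log) | Appointment date and attendance, both arms | No. The service is not named |
| Appendix P (medications) | Start and stop dates, both arms, baseline and end of study | Largely, for item 5 only |
| MBS/PBS data | Both arms, if the patient consented; intended for costing | Partial: drugs for item 5, and possibly rebated psychology sessions bearing on item 7 |

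Item 4 has no clear dated source. Item 7 has at best a partial one.

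**2. What does counting earlier care do to the comparison?**

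Notation, all values assumed because the protocol gives none:

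- q: share who had the care before randomisation, equal in expectation in both arms by randomisation
- u: in-trial rate among those without earlier care
- r: in-trial rate among those with earlier care

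True in-trial rate: T = q·r + (1 − q)·u.

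Rate recorded by an undated item: R = q + (1 − q)·u.

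Inflation in each arm: R − T = q·(1 − r).

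Change in the absolute difference: (R_I − R_C) − (T_I − T_C) = −q·(r_I − r_C).

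So the absolute difference shrinks only if the intervention raises in-trial care among previously treated patients (r_I above r_C). If r is the same in both arms and below 1, the difference is unchanged, but both rates rise by the same amount and the ratio moves toward 1.

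*Case A, earlier care independent of in-trial care (r = u), in-trial rates 70% and 40%.* The difference becomes (1 − q)·30 points. Power is for a two-sided 0.05 two-proportion z-test, as a guide only:

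Φ{[|Δ| − 1.96·√(2·p̄(1 − p̄)/n)] / √[(p_I(1 − p_I) + p_C(1 − p_C))/n]}.

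The protocol plans 75 per arm. The number with alcohol aetiology is not given, so 37 (about half of 75) is a second assumption.

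| q | Recorded rates | Difference (points) | Ratio | Power, 75/arm | Power, 37/arm |
|---|---|---|---|---|---|
| 0 (in-trial only) | 70% vs 40% | 30 | 1.75 | 96.5% | 74.7% |
| 0.2 | 76% vs 52% | 24 | 1.46 | 87.2% | 57.8% |
| 0.4 | 82% vs 64% | 18 | 1.28 | 70.3% | 41.3% |
| 0.6 | 88% vs 76% | 12 | 1.16 | 48.1% | 26.6% |
| 0.8 | 94% vs 88% | 6 | 1.07 | 24.8% | 14.4% |

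Example for q = 0.4: 0.4 + 0.6 × 0.70 = 0.82 and 0.4 + 0.6 × 0.40 = 0.64.

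*Case B, no effect among the previously treated.* Take q = 0.4, r = 0.40 in both arms, u = 0.70 and 0.40. True rates: 0.4 × 0.40 + 0.6 × 0.70 = 58%, and 0.4 × 0.40 + 0.6 × 0.40 = 40%, so the difference is 18 points and the ratio 1.45. Recorded rates: 82% and 64%, so the difference is still 18 points but the ratio is 1.28.

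The ratio is the scale on which the planned negative binomial model works, and it moves toward 1 in both cases.

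**The case against.** Several points on the other side are sound.

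- **Scoring is not fixed.** No section says that a Yes on items 4, 5 or 7 is the outcome. The derivation may be in an analysis plan that is not shown, and Appendix E also holds windowed or current-status items that bear on adherence and response. A reader might infer that earlier care is certain to be scored as trial care. The protocol does not support that; the point is conditional on these items being used.
- **The word *ever* is absent.** Appendix C and Appendix F item 2 print it where lifetime history is wanted, and Appendix E does not. To call these lifetime questions is therefore an inference. What stands is that the wording sets no start, so a respondent has no reason to leave earlier care out.
- **Yes may mean adherent.** A patient already linked to a service may need no new referral. This is fair, and it rules out a remedy that counts only first contacts, which would score continuing care as failure.
- **Some dates exist.** This is true for item 5 and partly for item 7, as shown above.
- **Appendix F.** A reader might extend the point to "Was the patient adherent to variceal bleeding prevention protocols (answer only at end of trial". That item is confined to the end of the trial, and the latest endoscopy date and the due dates stand beside it, so it reads naturally as adherence during the trial. It is not part of this point.
- **Appendix R.** Its item "How many ultrasounds has the patient had the last 2 years" has a window and dates, but it is not tied to randomisation. For a patient who leaves early it also reaches back before entry. It shows that a bounded item is feasible, and no more than that.

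**Conclusion.** The point holds for items 4 and 7 and, to a lesser extent, item 5. At end of trial these items cannot distinguish care before randomisation from care after it, and for items 4 and 7 the form gives no way to separate the two.

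If the items feed the alcohol-treatment measure, both arms' rates are inflated by q(1 − r). The ratio is pulled toward 1, provided that the intervention does not lower in-trial care among previously treated patients and that some of them receive none during the trial. The absolute difference shrinks as well if the intervention raises in-trial care in that group. A reader might infer that the difference always shrinks by the factor (1 − q). That needs earlier and in-trial care to be independent, which nothing in the protocol establishes.

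The size cannot be computed, because neither the share treated before nor any in-trial rate is given. The table is an illustration, and its power figures are not those of the planned model. They may also be optimistic: Appendix Q lists the end-of-study forms for patients who completed the study, and the Background cites 2-year survival of 60% and 35% in Child Pugh B and C.

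One measure among the secondary quality-of-care outcomes is affected, and the primary endpoint is not. The change is worth making because it is cheap and cannot be made after data collection.

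**What to change.** In the end-of-trial version of Appendix E:

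- Word items 4, 5 and 7 as *since randomisation*. Count any contact, prescription or referral in that period, including continuing care, and not only a first event.
- Add the date of the most recent such event to each item.
- Base the between-arm comparison of the alcohol-treatment measure on these in-trial events, with item 5 cross-checked against the start and stop dates in Appendix P.

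The cost is a few added fields. For controls, who have no contact with the trial nurses until the final interview, the answers will rest partly on patient report or case notes. Absolute percentages will be lower in both arms than the undated items would give.
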